### Random allocation

2.3

Before starting the study, a randomization list is produced using software-generated randomized numbers; the randomization depends on random blocks of 10 (Table 1). Patients will not know to which group they are assigned or which treatment they will be offered. Patients will be assigned at random to the ultrasound + LLLT group, LLLT group, or the ultrasound group. Participants are enrolled by the research assistant. After baseline examination, all patients will be given a full explanation of the treatment protocol and will be required to sign a written informed consent for study participation and for publication of the results. All the data collectors, surgeons, statistical analysts, as well as result assessors are not aware of grouping assignment (Fig. 1).

**Table 1 T1:** Patient baseline demographics.

Demographics	Combined group	LLLT group	Ultrasound group	*P* value
Number of patients (knees)				
Age at surgery^∗^ (years)				
Male sex (no. [%])				
BMI^∗^ (kg/m^2^)				
Right side (no. [%])				
Follow-up^∗^ (years)				

BMI = body mass index, LLLT = low-level laser therapy.

∗ The values are given as the mean and the SD.

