### Statistical analysis and power analysis

2.7

All analyses will be performed using SPSS for Windows, version 16, and GraphPad InStat. Analysis of variance is used for comparing mean values of patient's age, weight, height, and body mass index. For non-parametric measures like VAS and WOMAC, differences between baseline and post-treatment scores for each group are computed by the Wilcoxon signed ranks test. The difference between each treatment group is performed by the Kruskal–Wallis test. The level of statistical significance is set as *P* < .05. A power analysis is conducted to estimate the requisite sample size. From previous studies, a clinically significant difference reduction in the VAS was defined as 3 cm; a standard deviation of 3.49, probability of a Type I error of 0.05 and power of 0.8 resulted in an estimated sample size of 15. Consequently, a total of 120 subjects will be recruited.

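### The stated sample size of 15 fits no between-group comparison in this trial, and the target of 120 does not follow from it, although 120 is enough for a 3 cm difference

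*Protocol article*

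**What the plan says.** Section 2.7 (Statistical analysis and power analysis) gives the whole calculation in two sentences. The effect is described thus: "a clinically significant difference reduction in the VAS was defined as 3 cm". The other inputs and the result follow: "a standard deviation of 3.49, probability of a Type I error of 0.05 and power of 0.8 resulted in an estimated sample size of 15". The recruitment target is then presented as the consequence: "Consequently, a total of 120 subjects will be recruited". The Discussion repeats 120 without a derivation.

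The section does not say which test the calculation assumes, whether it is one- or two-sided, or whether 15 is per group or in total. It does not say whether 3 cm is a difference between groups or a fall from baseline, or whether 3.49 is the SD of scores or of changes.

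The design is nevertheless clear. Section 2.3 (Random allocation) has three arms: "Patients will be assigned at random to the ultrasound + LLLT group, LLLT group, or the ultrasound group". The Introduction expects a difference between intervention and control groups. Section 2.7 compares the arms as follows: "The difference between each treatment group is performed by the Kruskal–Wallis test". It also plans a Wilcoxon signed ranks test of baseline against post-treatment scores within each group.

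**The concern.** The article prints its inputs, its result and its conclusion, so the chain can be checked. It fails at both links. The inputs do not lead to 15 for a comparison of randomised groups, and 15 does not lead to 120 in a three-arm trial.

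The stated size and power are what a reader uses to judge what the trial can show. As printed, they do not describe the trial that will recruit 120 patients. A reader cannot tell what difference between two active treatments the trial can detect. That matters because both comparators are active, so the advantage of the combination over either one could well be smaller than 3 cm.

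**Working it through.** **Inputs, all from section 2.7:** difference 3 cm; SD 3.49; alpha 0.05; power 0.80. The standardised effect is d = 3/3.49 = 0.860.

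**Assumptions where the document is silent:** two-sided testing, because the Kruskal–Wallis test has no direction (one-sided is also shown); 15 read as per group (a total is also shown); equal allocation.

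**Step 1: try to reproduce 15 as a between-group size.** For two groups, by the normal approximation,

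n per group = 2 × [(z for alpha + z for power)/d]²

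- Two-sided: 2 × [(1.960 + 0.842)/0.860]² = 21.2, so 22. The t test gives 22.2, so 23 (power 79.5% at 22, 81.4% at 23).
- One-sided: 2 × [(1.645 + 0.842)/0.860]² = 16.7, so 17. The t test gives 17.5, so 18.
- Two-sided with Bonferroni for three pairs (normal approximation): 29.
- Three-group analysis of variance: about 62 in total if one group differs by 3 cm, about 82 if the third group lies midway.

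None of these gives 15.

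**Step 2: power if 15 were used.**

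| Reading of 15 | Power at 3 cm (t test) |
|---|---|
| 15 per group, two-sided | 62% |
| 15 per group, one-sided | 74% |
| 15 in total over two groups, two-sided | 34% |
| 15 in total over three groups (5 per arm), one pair, two-sided | 22% |

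In simulation with normal data and 15 per group, the Kruskal–Wallis test has about 62% power if one group differs and about 48% if the third lies midway.

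**Step 3: try to reproduce 15 as a within-group size.** A paired two-sided calculation gives n = [(1.960 + 0.842)/0.860]² = 10.6, so 11, or 12.7, so 13, by the t test. Dividing 12.68 by 0.864, the minimum relative efficiency of the Wilcoxon test, gives 14.7, so 15. The document mentions no such correction. This is the only route found that reaches 15.

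**Step 4: from 15 to 120.** 3 × 15 = 45 and 3 × 23 = 69. As a multiple, 120/15 = 8, which has no source in a three-arm design. As a dropout allowance, 120 would need 1 − 45/120 = 62.5% attrition from 45, or 1 − 69/120 = 42.5% from 69. None is stated.

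**Step 5: what 120 can do, assuming 40 per arm and SD 3.49 for the change in VAS (two-sided alpha 0.05).**

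- One pairwise contrast at 3 cm: 97% power by t test, about 96% by a rank test (simulation, normal data).
- Detectable difference at 80% power: 3.49 × √(2/40) × (1.960 + 0.842) = 2.19 cm, or about 2.2 cm.
- One pairwise contrast at 2 cm: about 72% by t test, about 69% by a rank test.
- Winning both contrasts of the combination against the single modalities (t tests, simulation): about 94% at 3 cm and about 58% at 2 cm. These two figures apply only if the sponsor adopts that rule; the article does not state it.

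**The case against.** The strongest reply is that 15 is not proven to be a miscalculation. The article never says the calculation was two-group, two-sided or per group. It speaks of a reduction in VAS, plans a signed ranks test within each group, and a paired calculation with an efficiency correction lands on 15. This stands in part: the defect may be a calculation for the wrong question and not a slip in arithmetic. It does not rescue the figure. A within-group size says nothing about the power of the randomised comparison, and 120 would still not follow from it.

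The second reply is that recruitment is fixed at 120, so power at 15 describes a trial nobody will run. That stands. A reader who sees 62% might infer that the trial is underpowered. The document does not support this: 120 exceeds the 66 to 69 needed for 3 cm with three equal groups.

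Third, 40 per arm is not in the article. No allocation ratio is given, and the blocks of 10 in section 2.3 do not divide equally among three arms. A rule of winning both contrasts is not in the article either, and only the sponsor can say what the 3 cm and 3.49 measure. All of this stands, and the figures in Step 5 carry those conditions.

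Finally, a journal article is condensed. But the point does not rest on omitted detail: the printed inputs, result and conclusion do not fit together.

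**Conclusion.** The sample-size statement is wrong as written for this design. No between-group reading that was tried gives 15; the two-sided requirement is 22 to 23 per group, about half as many again. The step from 15 to 120 is a non sequitur. The first conclusion rests on treating the between-group comparison as the trial's question, which the Introduction, the three-arm randomisation and the Kruskal–Wallis test all support. It does not depend on sidedness, since the one-sided requirement of 17 to 18 also misses 15.

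The consequence is limited. On the stated SD and equal arms, the trial has ample power for 3 cm and moderate power, about 69% to 72% per contrast, for 2 cm. What is lost is a true account of what the trial can detect. This should be fixed, but it does not put the recruitment target in doubt.

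**What to change.** Keep the total at 120. In section 2.7, delete the sample size of 15 and the word that presents 120 as its consequence, and replace them with a calculation for the between-group comparison. The sponsor should first confirm:

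- whether 3 cm is a difference between groups or a change from baseline, and whether 3.49 is the SD of scores or of changes;
- the allocation ratio;
- the test, its sidedness and the contrasts that the calculation covers;
- the actual basis for 120, including any dropout allowance.

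If the sponsor confirms equal arms, a between-group 3 cm and an SD of 3.49 for the change in VAS, the text could read: With 40 patients per arm (120 in total), two-sided alpha of 0.05 and an SD of 3.49 cm for the change in VAS, each pairwise comparison has about 97% power (about 96% with a rank test) to detect a difference of 3 cm; at 80% power the detectable difference is about 2.2 cm.

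If the claim will require the combination to beat both single modalities, that rule should be stated and its power given as well. If the confirmed inputs differ, the figures must be recalculated.

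The cost is a rewrite of two sentences and the sponsor's confirmation of the inputs. If they are as assumed here, no extra patients and no change of design are needed.

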## Discussion

3

The most frequent treatment for knee osteoarthritis is prescription painkillers and anti-inflammatory medications. Serious health risks are associated with these medications, including addiction and increased risk for gastrointestinal, renal, and cardiovascular problems. Ultrasound has been used as a noninvasive and safe physiotherapy for musculoskeletal conditions since its initial approval by the Food and Drug Administration for the treatment of fractures in 1994.^[14]^ Unlike other treatments, therapeutic ultrasound not only relieves osteoarthritis patient symptoms but has potential cartilage healing effects. LLLT is another widely used electrophysical agent for the control of musculoskeletal pain and modulation of the inflammatory process.^[15]^ It reduces the IL1-β and COX-2, thus reducing prostaglandin E2 levels, besides biomodulation of osteomyoarticular changes in osteoarthritic process, through photochemical and photobiological properties.^[16]^

To our knowledge, only Paolillo et al tried to evaluate the synergistic effects of ultrasound and LLLT in patients with knee osteoarthritis. However, the sample size of their study was too small to draw convincing conclusions, thus further research is needed to confirm the synergies.^[13]^ Therefore, we will conduct this present randomized double-blind study to evaluate the synergistic effects of simultaneously applying ultrasound plus LLLT on pain and muscle function in patients with knee osteoarthritis. It is assumed that there will be a remarkable difference in postoperative outcomes between the intervention and control groups. In our protocol, a total of 120 subjects will be recruited.
